## Abstract

**Background:**

Aging individuals are vulnerable to various Noncommunicable Diseases (NCDs). Different behaviors are closely related to a decreased risk of suffering from NCDs: sufficient Physical Activity (PA) (e.g., at least 150 mins Moderate-to-vigorous Physical Activity (MVPA) per week) and a healthy daily diet (e.g., at least five portions of Fruit and Vegetable Intake (FVI), 5–6 taels (189.0–226.8 g) Meat, Fish, Egg and Alternatives (MFEA)). Traditional face-to-face interventions were effective in behavior change. However, it was revealed to be resource-intensive and limited transfer due to poor self-regulation skills outside of face-to-face sessions. Thus, eHealth could be a supplement for older adults outside traditional face-to-face settings. The blended approach combining these two interventions might optimize the intervention effects on lifestyle behavior initiation and maintenance, but little research can be found among Hong Kong older adults. Therefore, the study aims to test a blended intervention to promote PA, diet, and health outcomes among Hong Kong community-dwelling older adults.

**Methods:**

This study will adopt a 10-week three-arm randomized controlled trial. The blended group will receive weekly (1) two 60-min face-to-face sessions with one for PA and one for diet, and (2) two web-based sessions with one for PA and one for diet. The face-to-face group will receive the same intervention content as the face-to-face sessions in the blended group. The control condition will receive a biweekly telephone call. The outcomes will include MVPA (minutes/week), FVI (portions/day), MFEA consumption (taels/day), social-cognitive factors (self-efficacy, planning, social support, action control), physical health outcomes (clinical indicators, senior physical fitness), mental health outcomes (depression, loneliness) and health-related quality of life. Data collection will be implemented at the pre-test, post-test, and 3-month follow-up test.

**Discussion:**

This is the first study evaluating a blended intervention promoting multiple health behaviors among Hong Kong community-dwelling older adults. If the effect of the blended intervention is superior to the traditional face-to-face group and the control group, it will enrich lifestyle intervention approaches and can be applied to older adults, helping them obtain health benefits. Furthermore, a better understanding of mechanisms will also have implications for theory-building.

**Clinical trial registration:**

https://www.isrctn.com/ISRCTN32329348, ISRCTN32329348.

## Introduction

1

Noncommunicable diseases (NCDs), such as cardiovascular diseases, cancer, diabetes, and obesity, are responsible for the mortality of approximately 41 million individuals annually, accounting for a staggering 74% of all global deaths (1). NCDs are of high prevalence due to a confluence of factors, including the globalization of unhealthy lifestyles and the demographic shift toward an aging population (2). Physical inactivity and unhealthy dietary patterns contribute to the manifestation of metabolic risk factors, such as elevated blood pressure, hyperglycemia, dyslipidemia, and obesity (3, 4). However, over one-quarter of adults were physically inactive, while over 3 million NCD-related deaths per year could be averted by increasing physical activity (PA) (5). The evidence indicates that 28% of adults were physically inactive and did not meet the World Health Organization (WHO) recommendation level of PA (5). The survey conducted in America suggested that the prevalence of physical inactivity significantly increases with age, with 26.9% among those aged 65–74 years and 35.3% among those aged ≥75 years (6). In Hong Kong, 24.8% of adults do not meet the WHO PA recommendation (at least 150 minutes Moderate-to-vigorous Physical Activity (MVPA) per week), while the percentage among older people is higher than that of other age groups (7).

Less than 50% of older adults adhere to the recommended five portions per day of fruit and vegetables (8, 9). An estimated 3.9 million deaths worldwide were attributable to inadequate fruit and vegetable consumption in 2017 (10). For Fruit and Vegetable Intake (FVI), most Hong Kong older adults consume less than five servings per day, in particular, 94.8% in the 65–74 age group, 96.6% in the 75–84 age group, and 99.3% in the 85 or above age group (7). As individual household incomes rise, global meat consumption and average *per capita* meat consumption are also increasing, driven by globalization and evolving food preferences, which heightened meat consumption is closely linked to the development of various diseases (11), particularly NCDs (12). It is essential to avoid excessive consumption of certain foods, such as meat consumption. In Hong Kong, the *per capita* meat consumption was 375 g, which ranked first in the world (13), while older people are recommended to have 5–6 taels Meat, Fish, Egg and Alternatives (MFEA) (189.0–226.8 g) per day (7). Engaging in multiple risk behaviors can lead to adverse health effects. Healthy lifestyle interventions among older adults are essential and meaningful to prevent harmful effects on individual health, medical systems, and medical costs (14).

Face-to-face workshops enable providers to deliver individualized interventions, facilitate interactive communication, and protect privacy (15). Empirical evidence supports the efficacy of face-to-face interventions in promoting health behaviors, such as PA and dietary choices (16, 17). Notwithstanding the practical support of face-to-face health interventions, this approach exhibits several limitations. Previous research also indicated significant barriers to older adults’ attendance and adherence to health behavior change intervention, including lack of perceived social support, low motivation, and poor self-regulation skills (18). The adherence rate of stand-alone face-to-face intervention on health promotion among older adults decreased over time (19).

eHealth is an emerging channel for delivering healthcare services and information through the Internet and associated technologies and media (e.g., computers and smartphones). It can complement face-to-face interventions for older adults in their homes or beyond traditional care settings (20). eHealth efficiently provides personalized feedback and long-term monitoring related to healthy lifestyles, which can enhance the maintenance of a healthy lifestyle over an extended period (21).

This study used the Health Action Process Approach (HAPA) model as a theoretical backdrop for the eHealth intervention (22). The HAPA model posited two phases (motivational and volitional) in the process of behavior change (23). During this dynamic process, individuals move from forming a behavioral intention to executing and sustaining a specific health behavior. In the process of behavioral change, several psychosocial factors play a crucial role. The motivational stage focuses on developing a behavioral intention, with action self-efficacy, outcome expectancies, and risk perceptions identified as contributing factors (24, 25). After individuals have established a behavioral intention, volitional factors such as action planning, coping planning, maintenance and recovery self-efficacies, and external resources like social support become essential in overcoming the intention-behavior gap (26). These factors collectively facilitate the execution and maintenance of the desired behavior (27). The widespread approval of the HAPA model in promoting various health behaviors among adults underscores its applicability (28). The effect of the techniques can be explained by theory, mainly relating to Behavior Change Techniques (27, 29).

However, eHealth intervention may also have disadvantages compared to face-to-face interventions. It demands specific skills, including electronic device functionality and reading comprehension proficiency. Providing individualized attention from professional medical care may pose challenges for caregivers (30). Furthermore, adherence is a crucial challenge in any eHealth intervention program, as many participants drop out before completion (31, 32).

In recent years, the blended intervention combining face-to-face workshops and eHealth intervention anticipates that the strengths of one delivery mode would offset the weaknesses of the other (33–36). A recent meta-analysis reported that the blended intervention can significantly promote total PA levels and diet behavior among adults (37). However, whether a blended intervention is more effective than traditional face-to-face interventions is unclear. Also, only limited findings reported the effectiveness of blended interventions in promoting PA and diet among older adults.

The findings of this study aim to fill the research gap, and its research design will be outlined in the following sections. There are two research objectives in this study. The primary aim is to compare the intervention effects between blended, face-to-face, and control groups in primary outcomes, including PA, diet (FVI and MFEA), and adherence to the health recommendations of PA and diet (FVI and MFEA). The second objective is to compare the intervention effects between blended, face-to-face, and control groups in secondary outcomes, including social-cognitive variables of behavior change (i.e., self-efficacy, planning, social support, and action control), physical health outcomes (i.e., clinical indicators, senior physical fitness), mental health outcomes (i.e., depression, loneliness), and health-related quality of life (HRQoL).

## Methods and design

2

### Study design and procedure

2.1

This study is a single-blind randomized controlled trial (RCT) comprising three groups: a blended face-to-face and eHealth intervention group (IG-1), a stand-alone face-to-face intervention group (IG-2), and a control group (CG). Evaluation will be conducted at pre-intervention (T1), post-intervention (T2), and 3 months follow-up after intervention completion (T3). The target population will be Hong Kong community-dwelling older adults. Participants will be recruited and randomly assigned into one of three groups. The intervention givers (i.e., PA coach and nutritionist) will be blinded from the assignment results to the intervention. The study process is presented in Figure 1.

**Figure 1 fig1:**
[figure not shown]
The flowchart of the study.

### Target population

2.2

Participants will be recruited from two Senior Centers in Hong Kong. The e-poster and video will be advertised by the staff in the Senior Centers. There are over 3,000 members in these two centers. Therefore, recruiting participants by advocating for the Senior Centers is feasible and advantageous. Potential study participants will be informed that there will be a health promotion program in which they can obtain health-related programs and receive a $300HKD (about $39USD) supermarket gift card as an incentive if the participants complete the 10-week health project and finish three times data collection.

Once the older adults express their interests, they will be encouraged to register in the program. After finishing all the registration and eligible screening, they will receive the study consent forms. The eligible criteria include: (1) aged 65 years and above; (2) owning a smartphone and having access to the Internet; (3) passing the Physical Activity Readiness Questionnaire (PAR-Q); (4) having sufficient reading and listening skills in Cantonese; (5) at least one health behavior (PA, FVI, MFEA) fails to meet the recommended health guideline. Exclusion criteria will include: (1) under special situations that seriously affected their diet (e.g., oral allergy syndrome) and mobility (e.g., physical disability); (2) meet all the health guidelines of PA, FVI, and MFEA; (3) participate in other ongoing project related to PA and diet intervention. Then, all participants will be allocated to one of three groups with an equal ratio (in a 1:1:1 ratio). The group allocation will be blinded. The researchers will provide the individual web link for the blended intervention group participants.

The sample size was calculated using G*Power 3.1 software. For achieving a medium effect size (Cohen’s *f* 0.26) on PA and diet based on a previous similar blended study among adults (35), with a statistical power (1-*β*) of 0.8 and an alpha of 0.05 (38), a total of 91 participants is required for the three groups (IG-1, IG-2, and CG). Considering the dropout rate of approximately 20% (35), a total of *N* = 114 participants is required to enable a robust evaluation.

### Intervention content

2.3

#### Face-to-face intervention group

2.3.1

Previous findings indicated that the majority of the face-to-face sessions conducted exercise training and education among older adults without theory backdrop (39). The participants in the face-to-face intervention group will engage in two 60-min sessions per week, including one session for PA at the gym and one for diet at the neighborhood senior center (40) for 10 weeks. Each PA session will consist of two parts: health education on PA and health (10 minutes) and physical exercise (50 minutes). Each session will include a warm-up exercise (5 minutes), a main exercise (40 minutes), and a cool-down exercise (5 minutes). The main activity will consist of diverse components such as aerobic training, resistance training, balance training, and mindfulness meditation training. The feedback will be given during PA courses if the participants have questions. Each PA session will be delivered by a PA coach with the assistance of two to four research helpers to ensure safety and feasibility.

Each diet session will consist of two parts: health education on diet (30 minutes) and nutrition counseling (30 minutes). The education topics, such as dietary fiber, cholesterol, fruits and vegetables, and red and white meat, were developed based on suggestions from a nutritionist. The nutrition counseling will include a 15 minutes group discussion with 3–4 participants in one group to design daily dishes and 15 minutes of dish sharing. Personalized nutritional advice will be offered by the nutritionist accordingly. Each diet session will be delivered by a nutritionist with the assistance of one research helper.

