### Data analysis

2.7

All data will be analyzed by using SPSS 29.0. The Expectation Maximization (EM) method will be applied for missing values. Intention-to-treat principles will be used for all analyses. Independent samples *t*-tests, *F*-tests, and Chi-square tests will be used to compare the baseline characteristics at T1. Statistical significance will be set at the 5% level (two-tailed).

A series of generalized linear mixed models (GLMM) will be applied to evaluate the intervention effects on behaviors (PA, FVI, and MFEA), social-cognitive variables of behaviors (i.e., self-efficacy, planning, social support, and action control), physical health outcomes (i.e., physical fitness test, clinical indicators), mental health outcomes (i.e., depression, loneliness), and health-related quality of life (HRQoL).

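### Both active arms are taught in shared classes, but the stated 80% power makes no allowance for clustering and the analysis section states no class term

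*Protocol article*

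**What the plan says.** Participants are recruited from two centres (section 2.2: "Participants will be recruited from two Senior Centers in Hong Kong") and allocated individually, 1:1:1.

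Section 2.3.1 describes one exercise session and one diet session a week for 10 weeks. On delivery it says "Each PA session will be delivered by a PA coach with the assistance of two to four research helpers", and on the diet session "The nutrition counseling will include a 15 minutes group discussion with 3–4 participants in one group to design daily dishes". Section 2.3.2 has the blended arm attend all the face-to-face sessions as well, and section 2.6 calls these sessions classes, with a check-in before each. Section 2.3.3 gives controls only a call of about 5 minutes every two weeks.

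The sample-size paragraph in section 2.2 lists four inputs: "For achieving a medium effect size (Cohen’s *f* 0.26) on PA and diet based on a previous similar blended study among adults", "with a statistical power (1-*β*) of 0.8 and an alpha of 0.05", and dropout of about 20%. It concludes that "a total of 91 participants is required for the three groups (IG-1, IG-2, and CG"), raised to 114. It mentions no ICC, class size or design effect.

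Section 2.7 says "A series of generalized linear mixed models (GLMM) will be applied" to behaviours and the secondary outcomes, at a two-tailed 5% level. It gives no random effects of any kind.

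**The concern.** This is a partially nested design. People in the same class share a coach, a nutritionist, fellow participants and joint meal planning for 10 weeks, while controls share nothing. The primary outcomes (accelerometer MVPA, fruit and vegetable intake, and meat, fish and egg intake) are behaviours that a good or poor class could plausibly move together.

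Two things are at stake. First, each active participant carries less independent information than the power calculation assumes. Second, an analysis without a class term would credit part of any class effect to the intervention and give intervals that are too narrow for active vs control. The primary aim compares all three arms, and the abstract says that superiority of the blended arm over both comparators would support wider application.

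**Working it through.** **Step 1. Reproduce the plan's own N.** Inputs from section 2.2: f = 0.26, alpha 0.05, power 0.80, dropout 20%. Three arms and three time points come from section 2.1. The article does not name the G*Power test. The variant that returns 91 is the repeated-measures within-between interaction with sphericity 1 and noncentrality λ = f² × N × (T − 1), where T is the number of time points:

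- λ = 0.0676 × 91 × 2 = 12.30; df1 = (3 − 1)(3 − 1) = 4; df2 = (91 − 3) × 2 = 176; power = 0.8015.
- At N = 90 the power is 0.796, so 91 is the smallest N that reaches 0.80.
- 91 / (1 − 0.20) = 113.75, rounded up to 114.

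The test variant is inferred from this match. No design effect is needed to reach either figure.

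**Step 2. Inputs for clustering.** Let m be the number of participants of one arm who share a class. Only one group size is stated: 3–4 in the diet discussion (3.5 used below). Classes of 10 and 19 are assumptions; 19 is half of an arm of 114 / 3 = 38, as if each arm had one class per centre. The ICC range 0.01–0.05 is also an assumption.

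**Step 3. Formulas** (large-sample normal approximation).

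- Design effect in an active arm: DE = 1 + (m − 1) × ICC. In control it is 1.
- Variance inflation for active vs control with equal arms: v = (DE + 1) / 2.
- Type I error if clustering is ignored: 2 × [1 − Φ(1.96 / √v)].
- Understatement of the standard error: 1 − 1/√v.
- Approximate power of the planned test at 91: as in step 1, with N in λ replaced by n + 2n/DE, where n = 91/3, and df2 kept at 176.

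Example, m = 10 and ICC = 0.05: DE = 1.45; v = 1.225; type I error = 7.7%; effective N = 30.33 + 60.67 / 1.45 = 72.2; power = 0.69.

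| m | ICC | DE | v | SE understated | Type I error, active vs control | Power at 91 |
|---|---|---|---|---|---|---|
| 3.5 | 0.01 | 1.025 | 1.0125 | 0.6% | 5.1% | 0.79 |
| 3.5 | 0.05 | 1.125 | 1.0625 | 3.0% | 5.7% | 0.77 |
| 10 | 0.01 | 1.09 | 1.045 | 2.2% | 5.5% | 0.78 |
| 10 | 0.05 | 1.45 | 1.225 | 9.6% | 7.7% | 0.69 |
| 19 | 0.01 | 1.18 | 1.09 | 4.2% | 6.0% | 0.75 |
| 19 | 0.05 | 1.90 | 1.45 | 17.0% | 10.4% | 0.62 |

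**Step 4. Blended vs face-to-face.** If, and only if, classes are specific to an arm, both sides are clustered and v = DE. For m = 10 and ICC 0.01, v = 1.09 and type I error is 6.0%. For m = 19 and ICC 0.05, v = 1.90 and it is 15.5%.

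**The case against.** The strongest objection is that section 2.7 states no random-effects structure at all. It does not even mention a participant effect, which repeated measures at T1–T3 would need, so its silence on class does not show that class is left out. A condensed article commonly leaves such detail to a full protocol or analysis plan. This stands. A reader might infer that the GLMM treats participants as independent and that the errors are too small as a matter of fact. The document does not support that, and the type I error figures hold only if no class term is fitted.

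Second, the clustering structure is largely unstated: number and size of classes, stability of membership, and whether the two active arms attend together. This also stands. The one stated group size, 3–4, moves the type I error very little, and those groups are not said to be fixed from week to week. The larger figures come from assumed class sizes.

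Third, a reader might infer that blended vs face-to-face is inflated too. The text does not settle this. Section 2.1 says that the coach and nutritionist are blinded to assignment, which is compatible with mixed classes, and in mixed classes the class effects would largely cancel in that comparison.

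Fourth, a reader might add the missing centre term to the charge. Centre membership precedes individual randomisation, so omitting it does not generally make treatment standard errors too small.

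None of this reaches the sample size. Its inputs and result are stated in full in the article, and they contain no allowance for clustering.

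**Conclusion.** The point holds in a limited form. It is established that delivery is by class in both active arms and individual in control, and that 91 and 114 follow from inputs that assume independent participants. The 80% power is therefore optimistic at any ICC above zero: about 0.77 with groups of 3.5, 0.69 with classes of 10 and 0.62 with classes of 19, all at an assumed ICC of 0.05.

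It is conditional that inference for active vs control is too liberal. That requires a GLMM without a class term and a positive ICC. The type I error is then between about 5.1% and 10.4% over the assumed ranges, and near the bottom of that range if the groups of 3–4 are the only source. For blended vs face-to-face, 6.0–15.5% applies only under arm-specific classes of 10–19, which the article does not describe.

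The approximations ignore the loss of degrees of freedom that comes with few classes. The point merits a change to the plan because the protection is cheap now and class membership may not be recoverable later.

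**What to change.** 1. Record each active participant's class at the check-in already planned before each session (section 2.6), and state the number and size of classes and whether the two active arms share them.
2. Fit class as a random effect in the active arms only, treating each control as a cluster of one, with small-sample degrees of freedom such as Satterthwaite.
3. At 38 per arm, classes of 10 to 19 give only about two to four per arm. If that is too few to estimate the class variance, report active vs control with standard errors inflated over a stated ICC range, for example 0.01–0.05, as a sensitivity analysis.
4. State in section 2.2 that the 80% power assumes no clustering, or restate it with a design effect. N can stay as it is, since the document gives neither ICC nor class size from which to justify another number.
5. A fixed effect for centre is an optional precision adjustment, not a correction for understated errors.

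The cost is one recorded variable, one model term and a sentence on power. Intervals for active vs control will widen, possibly considerably if there are few classes.

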#### Face-to-face and eHealth blended intervention group

2.3.2

In addition to attending all face-to-face sessions, participants in the blended intervention group will participate in a theory-based and web-based behavioral change promotion eHealth intervention, including one program for PA and one program for diet each week. A mobile-based website, namely Perfect Diet and Exercise (in Cantonese: “食” 全十美, 行大 “運”), will be established to facilitate the intervention. The website’s homepage will have the PA module and the diet (FVI and MFEA) module. Participants can access each module to take part in respective online learning activities. Each module will consist of two sections. Section 1 comprises a theory-based 10-week intervention program targeting social-cognitive predictors of PA/diet (FVI and MFEA). Participants will access this section once a week. Section 2 is a data repository platform collecting former exercises and incentive activities. Participants can access their files at any time throughout the 10-week intervention period, including behavior records of PA/diet, action planning of PA/diet, coping planning of PA/diet, and “my diary” about PA/diet behaviors. The weekly eHealth intervention component will be developed based on the Health Action Process Approach (HAPA) (41). Following the HAPA-based social-cognitive variables, the weekly intervention content will be designed accordingly (see Table 1).

**Table 1 tab1:** Theory-based intervention variables and behavior change techniques (BCTs) in 10 weeks.

Time	Social-cognitive variables	Behavior change techniques (BCTs)	BCTs related strategies
Week1	Motivational self-efficacy Action planning Social support	1.4 Action planning 2.2 Feedback on behavior 3.2 Social support practical 3.3 Social support emotional 7.1 Prompts/cues 15.1 Verbal persuasion about capability	a) Asking participants about their MVPA/diet behavior and providing personally tailored feedback b) Prompting verbal persuasion about the capability of performing MVPA/diet (targeting motivational self-efficacy) c) Asking participants to keep their plan in mind can help them successfully perform the wanted behavior (targeting Action control) d) Giving examples of successful action plans for MVPA/diet adherence (targeting action planning) e) Asking participants to make specific action plans of when, where, and how to perform MVPA/diet (targeting action planning) f) Asking participants to review social support on MVPA/diet initiation they received and give examples of successful social support for MVPA/diet adherence (targeting perceived social support)
Week 2–4	Motivational self-efficacy Action planning Social support	1.4 Action planning 2.2 Feedback on behavior 3.2 Social support practical 3.3 Social support emotional 7.1 Prompts/cues 15.1 Verbal persuasion about capability	Some strategies used in Week 1 (a, b, c, d, f) will be further applied in Week 2–4 g) Giving examples of successful cases of MVPA/diet participation (further targeting motivational self-efficacy) h) Participants will be asked to access the execution of action plans and adjust the previous action plans if necessary (targeting revision of action planning)
Week 5	Volitional self-efficacy Coping planning Action control Social support	1.2 Problem solving (coping panning) 2.2 Feedback on behavior 2.3 Self-monitoring of behavior 3.2 Social support practical 3.3 Social support emotional 7.1 Prompts/cues 10.1. Material incentive behavior 15.1 Verbal persuasion about capability	Some strategies used in Week 1–4 (a, b, d, f) will be further applied in Week 5 i) Giving examples of successful cases of MVPA/diet maintenance and recovery (targeting VSE) j) Giving examples of successful coping plans for MVPA/diet maintenance and recovery (targeting coping planning) k) Providing guidance (e.g., If-then algorithm) on how to set coping plans to overcome potential barriers when performing MVPA/diet (targeting coping planning) l) Guiding how to write a reflective diary (MVPA/diet behavior performed and emotional experience) to record and self-monitor their daily MVPA/diet (targeting action control)
Week 6–10	Volitional self-efficacy Coping planning Action control Social support	1.2 Problem solving (coping panning) 2.2 Feedback on behavior 2.3 Self-monitoring of behavior 3.2 Social support practical 3.3 Social support emotional 7.1 Prompts/cues 10.1. Material incentive behavior 15.1 Verbal persuasion about capability	Some strategies used in Week 1–5 (a, b, d, f, l) will be further applied in Week 6–10 m) Participants will be asked to review the execution of coping plans and adjust the coping plans in Weeks 6–9 if necessary (targeting revision of coping planning)

In addition, the intervention will apply different behavior change techniques (BCTs) to facilitate behavior (42). The detailed strategies of BCTs are presented in Table 1. For example, the participants will receive two types of feedback in the weekly web-based health session. This will include individualized feedback on their behavior performance in the 1st week, 2nd week, 3rd week, 4th week, and 5th week, respectively. Furthermore, the normative feedback on the criterion-based behavior recommendations (e.g., accumulated at least 150 minutes with moderate intensity of PA per week, five portions of FVI per day, 5–6 taels of MFEA per day) (see Figure 2) will be contained.

